### Interim analyses {21b}

The investigation of this study will be completed in one phase.

### Methods for additional analyses (e.g., subgroup analyses) {20b}

Subgroup analyses will be conducted based on age and sex. Furthermore, as we collect additional data on physical activity through a global physical activity questionnaire (GPAQ), a subgroup analysis will be conducted on the relationship between daily life physical activities and the study outcomes.

### Methods in analysis to handle protocol non-adherence and any statistical methods to handle missing data {20c}

In this study, we will conduct an intention-to-treat analysis, including data from all participants, even those who drop out. To address missing values, we will apply the multiple imputation method and a machine learning approach, such as random forest.

### Plans to give access to the full protocol, participant-leveldata, and statistical code {31c}

All data and statistical codes can be provided by the corresponding author upon request. In this case, personal details will be anonymized and cannot be tracked from the provided dataset.

### Oversight and monitoring

#### Composition of the coordinating center and trial steering committee {5d}

The study protocol and researchers involved are under the supervision of the Ethics Committee of Tohoku University Graduate School of Medicine. The principal investigator will manage the study implementation and collected datasets. The principal investigator’s responsibilities include participant recruitment, ensuring data quality, and participant follow-up. Any modifications to the study protocol or occurrence of adverse events will be promptly reported to the Ethics Committee. The study team convenes weekly meetings to discuss the trial’s progress.

### Composition of the data monitoring committee, its role, and reporting structure {21a}

There are no specific committees for data monitoring. The researchers responsible report any issues and adverse events to the Ethics Committee through monitoring processes.

### Adverse event reporting and harms {22}

Adverse events must be reported to an Ethics Committee. Representative researchers are required to confirm the details of each event. These events are graded according to the Japanese version of the National Cancer Institute Common Terminology Criteria (CTCAE) for Adverse Events v4.0. If an adverse event occurs, the researcher must immediately contact the medical staff to ensure prompt and appropriate treatment of the affected participant. Based on the study population and intervention characteristics, anticipated harms include fatigue, dizziness, and headache, which will be systematically monitored through participant self-reports. Any unexpected adverse events will be recorded on an as-occurs basis and reported as necessary, with collection occurring non-systematically through spontaneous participant reporting or clinician detection. For reporting purposes, all adverse events of CTCAE grade 3 or higher will be documented in full, while lower-grade adverse events will be reported based on their frequency and clinical relevance.

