**Fig. 1 Fig1:**
[figure not shown]
Circuit training procedure

Resistance training includes 12 types of exercises (chest press/seated row, squat, shoulder press/lat pull, leg extension/leg curl, abdominal crunch/back extension, lateral lift, elbow flexion/extension, horizontal leg press, pectoral deck, oblique, hip abductor/adductor, and gluteus). Under the instructions of qualified instructors, the participants will perform machine-based resistance training. The machines depend on calibrated pneumatic resistance pistons. In the circuit training, participants will perform as many repetitions as possible in a 30-s time period. During the rest periods, participants will perform floor-based aerobic exercises (e.g., running or skipping in place) on a stepboard.

In the waitlist control group, participants will continue to perform their ordinary daily life activities as usual and not join any new exercise clubs or gyms during the study period. Since one purpose of this study is to evaluate exercise as a supporting tool for brain health in sedentary adults, we will compare the lifestyles of those who remain sedentary with those who begin a new active lifestyle (i.e., long-term combined interval training). Thus, no active control group is recruited for this study.

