### Criteria for discontinuing or modifying allocated interventions {11b}

Participants have the right to withdraw from the study at any time after submitting a withdrawal form. The intervention will be discontinued when participants have difficulty maintaining exercise training because of injury or pain.

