### Strategies to improve adherence to interventions {11c}

The participants in the intervention group will engage in circuit training sessions alongside regular exercisers. This setup allows for interaction and social bonding, which can enhance the participants’ experience and potentially reduce dropout rates by creating a supportive community environment. Such social connections are crucial, as they provide encouragement and a sense of belonging, which are important factors in maintaining consistent participation in the program. Exercise adherence will be systematically monitored through weekly attendance tracking of circuit training sessions and regular follow-up communication (phone or email) with participants who miss consecutive sessions to verify their well-being and address potential barriers. When applicable, participants will also complete brief workout logs documenting perceived exertion and session details.

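### Injury and pain are foreseen as the reason for stopping the exercise but are not among the harms named for systematic monitoring

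*Protocol article*

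**What the plan says.** Two sections of the protocol article deal with harms from the exercise.

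- **Criteria for discontinuing or modifying allocated interventions {11b}:** "The intervention will be discontinued when participants have difficulty maintaining exercise training because of injury or pain". Apart from the general right to withdraw, no other harm-related ground is named.
- **Adverse event reporting and harms {22}:** "anticipated harms include fatigue, dizziness, and headache, which will be systematically monitored through participant self-reports". For unexpected events the same section provides a different route, "with collection occurring non-systematically through spontaneous participant reporting or clinician detection". Events of CTCAE grade 3 or higher are documented in full, whereas "lower-grade adverse events will be reported based on their frequency and clinical relevance".

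The contacts described between the two assessments are these.

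- **Exercise arm:** Under Intervention description {11a}, below Fig. 1, "Under the instructions of qualified instructors, the participants will perform machine-based resistance training". Under Strategies to improve adherence {11c}, attendance is tracked weekly and there is "regular follow-up communication (phone or email) with participants who miss consecutive sessions to verify their well-being". The retention section {18a} adds rescheduling by e-mail or telephone and regular reminder e-mails about the coming week's class.
- **Control arm:** "participants will continue to perform their ordinary daily life activities as usual and not join any new exercise clubs or gyms". No scheduled contact between baseline and week 16 is described.

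**The concern.** The protocol anticipates injury or pain in one section. In another, it leaves them off the only list of harms that it undertakes to ask about. The list is said to be derived from the study population and the characteristics of the intervention. That population is women aged 40 to 74 who do not exercise regularly at gyms or sports clubs. The intervention is maximal repetitions on resistance machines in 30-second bouts, alternating with running or skipping on a stepboard. Musculoskeletal complaints belong naturally on such a list.

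At stake is the quality of the harms record. Solicited and unsolicited events are not captured equally well, so a low count of strains or joint pain next to a higher count of headaches could partly reflect how each was collected. The reporting rule adds to this. Whether an event below grade 3 is reported depends partly on its frequency, and for unsolicited events that frequency comes from non-systematic collection. If one arm has more contact with study staff than the other, the counts by arm are also harder to interpret.

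**Working it through.** The article states no harm rate or capture rate, so there is no figure of its own to reproduce. The check sets the sections side by side and then asks whether the effect could be quantified.

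**Step 1: which route applies to injury and pain?** Section {22} offers two.

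| Route | Events covered | Method |
|---|---|---|
| A | Anticipated harms; fatigue, dizziness and headache are named | Systematic self-report |
| B | Unexpected events | Spontaneous report or clinician detection |

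Section {11b} foresees injury and pain, so they do not fit route B as unexpected events. They are also not named in route A. Staff who follow the text literally would ask about three symptoms and record injury or pain only if it is mentioned or noticed.

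**Step 2: does another section fill the gap?**

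- *SF-36 bodily pain* (Quality of life section) is measured in both arms at baseline and week 16. It is a quality-of-life domain and does not record adverse events.
- *Reasons for dropping out* (Data management {19}) are specified and reported, but this misses women who are injured and stay in the study.
- *Discontinuation under {11b}* brings to notice only those injuries or pains that make training difficult.

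Each gives partial information. None asks about injury or pain as an adverse event.

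**Step 3: is contact equal between arms?** Instructor-led sessions, attendance tracking, calls or e-mails after missed sessions, rescheduling and reminders are all tied to the exercise sessions. The article describes nothing comparable for controls. The trial is open-label, so all parties know the allocation.

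**Step 4: can the effect be sized?** Let n be the number per arm, p the true risk (taken as equal in both arms) and c the proportion of events captured. Recorded events = n × p × c, and the recorded risk ratio = c(exercise) / c(control). Take n = 25, about half of the planned 51, and assume p = 20%, which gives 25 × 0.20 = 5 true events per arm. All values of p and c below are assumptions.

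| c exercise | c control | Recorded, exercise | Recorded, control | Recorded ratio |
|---|---|---|---|---|
| 0.3 | 0.4 | 5 × 0.3 = 1.5 | 5 × 0.4 = 2.0 | 0.75 |
| 0.5 | 0.5 | 2.5 | 2.5 | 1.0 |
| 0.7 | 0.4 | 3.5 | 2.0 | 1.75 |
| 0.8 | 0.4 | 4.0 | 2.0 | 2.0 |

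With no true difference, the recorded ratio runs from 0.75 to 2.0 according to the capture rates chosen. With equal capture of 50%, half the events are lost but the ratio is unbiased. The table shows only that the result depends entirely on quantities the document does not give. It is not an estimate for this trial.

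**The case against.** The strongest case on the other side has five parts.

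1. **The list may be open.** The word *include* can introduce examples, and only unexpected events are sent to the non-systematic route. Injury and pain are foreseen, so they could be meant to fall under systematic monitoring. This is a fair reading, but the text does not say so, and the three symptoms are the only ones it commits to. The ambiguity itself needs resolving.
2. **Controls do have a route.** A reader might infer that an event in a control participant cannot reach the investigators before week 16. The documents do not support that. Spontaneous reporting is not limited by arm, and the oversight section gives the principal investigator responsibility for participant follow-up without limiting it to one arm. What is absent from the description is a prompt.
3. **Supervision may catch most injuries in the exercise arm.** Instructors, missed-session follow-up and the discontinuation criterion all help, and events of grade 3 or higher are documented in full. It therefore cannot be said that injuries will be undercounted, only that less complete capture is likely.
4. **The article is condensed.** The symptom form, any instructor reporting chain and the contact schedule for controls may be in the full protocol or in Table 1 and Fig. 2, which are not shown. Their absence here is not a fault. This point stands, and it limits the unequal-capture concern to a possibility.
5. **No between-arm harms analysis is planned.** The statistical sections describe none. A reader might infer that the trial could therefore not support its description of the programme as accessible and feasible. That goes too far: the article uses those terms mainly of the 30-minute session length and integration into daily life, not as a safety conclusion.

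The mismatch between {11b} and {22} remains after all five.

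**Conclusion.** The point holds as an internal mismatch that is cheap to repair. Section {11b} foresees injury or pain as the harm-related reason for discontinuing the exercise. Section {22} does not name them among the systematically monitored harms, and its only other route is non-systematic and meant for unexpected events. Read as written, musculoskeletal injury and pain are likely to be captured less completely than fatigue, dizziness and headache. Capture may also be unequal between arms, because the between-visit contacts described are with the exercise arm.

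The size and direction of any bias cannot be computed from the document. The conclusion rests on two assumptions: that staff solicit only the symptoms named, and that solicited events are recorded more fully than unsolicited ones. It is tempting to call injury the main risk of the programme, but the article does not rank its risks. The primary efficacy analysis is unaffected.

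**What to change.** Reconcile {11b} and {22}. In {22}, add musculoskeletal injury or pain, and falls, to the harms that are systematically monitored. Falls are not named in the article; they are suggested because the programme includes running or skipping on a stepboard. Put the same questions, with the same wording and recall period, to both arms, at least at the week-16 visit that both already attend. If the full protocol already solicits these harms, one sentence in {22} saying so is enough.

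The change concerns how harms are recorded and leaves the discontinuation criterion and the exercise programme as they are. It costs a few extra questions on an existing form, and more minor events to record and grade.

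If the week-16 visits have already begun, introduce the questions in both arms from the same date and state that date when harms are reported.

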### Frequency and plans for auditing trial conduct {23}

The Ethics Committee is supervising this trial, as previously mentioned. However, plans for audit are not integrated into this study. When the study protocol changes or adverse events occur, the researchers will report the results to the Ethics Committee.

### Research ethics approval {24}

This study was approved by the Ethics Committee of Tohoku University School of Medicine (research ID: 2023–1–1016). Our study design was registered with the University Hospital Medical Information Network (UMIN-CTR, UMIN000053937).

### Plans for communicating important protocol amendments to relevant parties (e.g., trial participants, ethical committees) {25}

Any modifications to the study protocol are reported to the Ethics Committee and require their approval. Documents relevant to informed consent will reflect the modifications. Furthermore, if necessary, the principal investigator will notify the participants about the modifications.

### Dissemination plans {31a}

The findings of this study will be presented in peer-reviewed journals and at academic conferences.

## Discussion

This study provides the first insights into the effects of long-term circuit training on cognitive function through comprehensive perspectives on the gut microbiota, cytokines, and proteins involved in aging control. As a secondary aim, we identify the factors associated with the beneficial effects of exercise on cognitive function. Furthermore, this study examines the relationship between the beneficial effects of exercise, psychological characteristics, and mental health. Although most studies have highlighted the benefits of long-term exercise on cognitive function, they have not explored these broader perspectives. The potential impact of these benefits encourages engagement in physical activity for brain and mental health, particularly in the aging population. Clarifying these effects and relationships could pave the way for further understanding of the potential effects of exercise on cognition.

Considering the relationship between exercise and gut microbiota, long-term exercise modulates the environment of the gut microbiota and creates appropriate environments to promote the secretion of growth factors, such as BDNF [73]. This study aims to unveil the association between exercise-induced modulation of the gut microbiota and growth factors. Growth factors have also been suggested to stimulate aging control [7]. The activation of mTOR and SIRT has been proposed to promote neural plasticity [7, 74], potentially leading to improvements in cognitive performance. Thus, the beneficial effects of circuit training on cognitive function may be rooted in the communication between the gut, aging control factors, and growth factors.

From a different perspective, Nouchi and Nouchi [75] discovered that circuit training exercises increase vigor-activity mood scores in middle-aged and older populations. Thus, based on a previously established association, long-term combination exercise may alter psychological characteristics and improve mental health [76–78]. Furthermore, it is expected that the gut microbiota and factors controlling aging are involved in psychological characteristics and mental health. This study plans to use SEM analysis to unravel the complex relationships between exercise, gut microbiota, aging control factors, cytokines, and proteins involved in neuroplasticity and aging control, psychological characteristics, mental health, and QOL. Elucidating these causal relationships can help reveal the potential effects of circuit training exercises on aging populations.

Nonetheless, a notable limitation of this study is the lack of dietary intake monitoring. While this approach reflects a real-world setting where participants maintain their usual dietary habits during the exercise intervention, it may limit our understanding of the relationship between exercise and changes in gut microbiota. Future research should consider incorporating dietary controls to better understand how dietary patterns might influence the gut microbiota response to exercise.

Our findings advance the current understanding of exercise-induced cognitive enhancement in several important ways. First, we integrate exercise science, gut microbiota analysis, and aging research to demonstrate how shorter-duration circuit training (30 min) can effectively promote cognitive health through multiple physiological pathways. Second, our exploratory analyses of gut microbiota and protein expression provide novel insights into the potential mechanisms through which circuit training may influence cognitive function, opening new avenues for future research in exercise neuroscience. Finally, by delineating the relationship between exercise adherence, grit, and resilience using SEM, we offer practical implications for developing sustainable exercise interventions that can be readily adopted in daily life. These insights could inform future intervention studies aimed at preventing cognitive decline in aging populations while ensuring practical feasibility in real-world settings.

In summary, this study aims to clarify the effects of long-term circuit training exercises on executive and memory functions from a comprehensive perspective. These findings address age-related cognitive decline from the perspective of exercise. In developed countries, including Japan, cognitive decline exerts upward pressure on healthcare costs. Additionally, diminished cognitive function is likely linked to deterioration of mental health and QOL. Although numerous studies have suggested that long-term exercise is a preventive tool against cognitive decline, the comprehensive relationship between exercise, the gut, aging, and the brain remains unclear. To date, the beneficial effects of exercise have not been sufficiently emphasized to encourage the middle-aged and older populations to engage in exercise to improve their brain health. Initiating physical exercise is a significant obstacle, particularly in sedentary populations. We have designed our study protocol considering these factors. We believe that our findings will contribute to addressing the issue of cognitive decline in aging populations by providing valuable insights and potentially guiding interventions.

## Trial status

Patient recruitment began in June 2024 and is anticipated to be completed by February 2025. The current protocol is version 2.0. This trial is currently underway in our laboratory.

## Abbreviations

BDNF: Brain-derived neurotrophic factor
IGF-1: Insulin-like growth factor
mTOR: Mechanistic target of rapamycin
SIRT: Sirtuin genes
SCFAs: Short-chain fatty acids
HR: Heart rate
SEM: Structural equation modeling
LMM: Linear mixed model
GPAQ: Global Physical Activity Questionnaire
POMS: Profile of Mood States
QOL: Quality of life
